## **3. Subjects**

3.1. Subjects

Japanese

Healthy volunteers

Members or employees of Seirei Hamamatsu General Hospital

3.2. Inclusion criteria

No ocular pathologies detected by slit-lamp biomicroscopy and fundus ophthalmoscopy

Visual acuity of 0.8 or better at the time of the MPOD measurement

A spherical equivalent refractive error of less than -6.0 dioptor

No gastrointestinal diseases that could cause disturbance of dietary absorption

No diabetes

No history of lutein supplementation

No allergy to lutein and zeaxanthin

No history of smoking at least within one year

## 3.3. Exclusion criteria

Eye with cataract to the degree having substantial effects on the measurement of the macular pigment density

Eye of which mydriatic pupil diameter is less than 6.5 mm

Other subject assessed ineligible by the investigator

## 3.4. Number of subjects planned

Thirty-six patients in total (table 1)

Table 1 Number of subjects

|  | | Xanmax | | FlorGLO | | total |
| --- | --- | --- | --- | --- | --- | --- |
|  |  | M | F | M | F |  |
| Young age group | 20-34 yr | 3 | 3 | 3 | 3 | 12 |
| Middle age group | 35-49 yr | 3 | 3 | 3 | 3 | 12 |
| Senile age group | 50-64 yr | 3 | 3 | 3 | 3 | 12 |
| total | | 9 | 9 | 9 | 9 | 36 |

# 4. Study protocol

## 4.1. Study design

Randomized, double-blind, parallel-group comparison study in a single institute

## 4.2. Study procedures

Investigators perform history taking and ophthalmological examination ( measurement of visual acuity, measurement of intraocular pressure, fundoscopic and slit-lamp biomicroscopic observation under mydriasis) and evaluate whether the subjects admit the inclusion or exclusion criteria. Supervisory investigator determines the subject eyes.

All subjects received explanation on the detail of this study and signed an informed consent form. After obtaining written informed consent, subject number was assigned to each one in order to the enrollment.

The supervisory investigator will prepare and store the table covering the subject number, subject name, original medical record ID, date of consent, and date of start of administration.　(table 2).

Table 2 Subject records

|  | name | ID | Date of consent | Date of study start |  | name | ID | Date of consent | Date of study start |
| --- | --- | --- | --- | --- | --- | --- | --- | --- | --- |
| Y-male1 |  |  |  |  | Y-female1 |  |  |  |  |
| Y-male2 |  |  |  |  | Y-female2 |  |  |  |  |
| Y-male3 |  |  |  |  | Y-female3 |  |  |  |  |
| Y-male4 |  |  |  |  | Y-female4 |  |  |  |  |
| Y-male5 |  |  |  |  | Y-female5 |  |  |  |  |
| Y-male6 |  |  |  |  | Y-female6 |  |  |  |  |
|  | | | | | | | | | |
| M-male1 |  |  |  |  | M-female1 |  |  |  |  |
| M-male2 |  |  |  |  | M-female2 |  |  |  |  |
| M-male3 |  |  |  |  | M-female3 |  |  |  |  |
| M-male4 |  |  |  |  | M-female4 |  |  |  |  |
| M-male5 |  |  |  |  | M-female5 |  |  |  |  |
| M-male6 |  |  |  |  | M-female6 |  |  |  |  |
|  | | | | | | | | | |
| S-male1 |  |  |  |  | S-female1 |  |  |  |  |
| S-male2 |  |  |  |  | S-female2 |  |  |  |  |
| S-male3 |  |  |  |  | S-female3 |  |  |  |  |
| S-male4 |  |  |  |  | S-female4 |  |  |  |  |
| S-male5 |  |  |  |  | S-female5 |  |  |  |  |
| S-male6 |  |  |  |  | S-female6 |  |  |  |  |

### 4.3 Ophthalmological examinations

Measurement of far and near visual acuity, Measurement of contrast/glare sensitivity, Focal electroretinography (macular ERG), Optical coherence tomography (OCT), Color fundus photography, Measurement of MPOD

Measurement of MPOD

Make the subject eye mydriatic by the instillation of the mydriatic eye drop. Measure the pupil diameter. It is desirable that subjects have at least 7.0 mm of the mydriatic pupil diameter. Exclude the subject having the mydriatic pupil diameter of less than 6.5 mm.

Use the resonance Raman spectroscopy for the measurement. On each day of measurement, perform the pretest measurement using the standard device and retain the record.

Perform three repetitions of measurement per eye and retain all measurement data in the original medical record.

4.4 Measurement of the plasma lutein level

Obtain about 2 mL of venous blood using the heparin-added vacuum blood collection tube. Centrifuge the blood sample (4°C, 3000 rotations, 15 minutes) immediately and collect each exactly half of obtained plasma to two sample tubes. Freeze-store the plasma samples at the temperature of -20°C or under until they are submitted to the analysis center.

Diagnostic Division of Otsuka Pharmaceutical Co.,Ltd.

[name]

[contact]　 [contact]

4.5. Study schedule

Study schedule follows table 3.

## Table 3 Study schedule

|  | Explanations and obtainment of consent, enrollment (start of intake from the next day) | 1m | 2m | 3m | 4m | 5m | 6m |
| --- | --- | --- | --- | --- | --- | --- | --- |
| Visual acuity | ○ |  |  | ○ |  |  | ○ |
| Contrast・Glare sensitivity | ○ |  |  | ○ |  |  | ○ |
| Macular ERG | ○ |  |  |  |  |  | ○ |
| OCT | ○ |  |  |  |  |  | ○ |
| Fundus photography | ○ |  |  |  |  |  |  |
| Macular pigment measurement | ○ | ○ | ○ | ○ | ○ | ○ | ○ |
| Blood sample collection | ○ |  |  | ○ |  |  | ○ |

4.6. Assignment of the investigational supplement

The assignment personnel will prepare the table to assign the subjects with two supplements, FloraGLO and Xanmax corresponding to the subject number. The number of subjects assigned each supplement has to be equal between men and women. For example, in the group of young men, three men are assigned FloraGLO and three Xanmax.

Table 4. Example of allocation (The actual assignment is different from this)

|  | Investigational  food |  | Investigational  food |
| --- | --- | --- | --- |
| Y-male1 | Xanmax | Y-female1 | FloraGLO |
| Y-male2 | Xanmax | Y-female2 | Xanmax |
| Y-male3 | FloraGLO | Y-female3 | FloraGLO |
| Y-male4 | FloraGLO | Y-female4 | Xanmax |
| Y-male5 | Xanmax | Y-female5 | Xanmax |
| Y-male6 | FloraGLO | Y-female6 | FloraGLO |
|  |  |  |  |
| M-male1 | Xanmax | M-female1 | FloraGLO |
| M-male2 | FloraGLO | M-female2 | Xanmax |
| M-male3 | Xanmax | M-female3 | Xanmax |
| M-male4 | FloraGLO | M-female4 | FloraGLO |
| M-male5 | FloraGLO | M-female5 | FloraGLO |
| M-male6 | Xanmax | M-female6 | Xanmax |
|  |  |  |  |
| S-male1 | Xanmax | S-female1 | FloraGLO |
| S-male2 | Xanmax | S-female2 | Xanmax |
| S-male3 | Xanmax | S-female3 | FloraGLO |
| S-male4 | FloraGLO | S-female4 | Xanmax |
| S-male5 | FloraGLO | S-female5 | FloraGLO |
| S-male6 | FloraGLO | S-female6 | Xanmax |

The assignment personnel will prepare the investigational food according to the allocation table, and send them to the supervisory investigator. The subject number has to be written clearly on each investigational food. Thus, only assignment personnel knows the kind of investigational food assigned to each subject, and the supervisory investigator, investigators, examiners and subjects do not know the kind of investigational food.

# 4.7. Investigational food

1. Xanmax lutein:

One capsule contains 10 mg of lutein and 1mg of zeaxanthin. Suspension is safflower oil.

1. FloraGLO lutein (DSM Co.Ltd):

One capsule contains 10 mg of lutein and 0.05mg of zeaxanthin. Suspension is corn oil.

## 4.8. intake of supplement

The subjects will take one capsule once a day after meals with water according to the allocation.

4.9. Administration period

Six months

# 5. Discontinuation criteria and procedures

## 5.1. Discontinuation criteria

Discontinue the study in the individual subject if the subject meets the following subject-specific discontinuation criteria. Discontinue the whole or part of the study if the discontinuation criteria apply.

The following discontinuation criteria are determined to secure the safety of the subjects and from the ethical viewpoint.

### 5.2. Discontinuation criteria for individual subjects

1. If the subject withdraws the consent or requests the discontinuation
2. If the subject turns out not able to undergo the scheduled examinations/observations for the subject's own reason after the start of the study
3. If the study is suspended for the subject's own reason (e.g. transfer, change of doctor/hospital, business, inability of follow)
4. If the investigator assesses it difficult to continue the study because of the AE that has taken place after the start of the study
5. If the subject turns out to be ineligible after the start of the study
6. If the subject turns out not to have taken the investigational food as instructed by the investigator
7. In the event of onset of an incidental accident
8. If otherwise the investigator assesses the subject to be ineligible for the study

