## 5.4 Procedures to follow after the discontinuation

1. Take measures necessary after the discontinuation. When the study is discontinued because of the AE, the investigator must take measures as appropriate irrespective of the reason.
2. For no show of unknown reason, the investigator will never fail to contact the subject within 4 weeks after the scheduled last administration to solicit the visit and investigate the outcome.

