# 9. Evaluation (note; The number is mistaken in the original protocol written in Japanese)

## 9.1. Primary variable

Changes in the macular pigment optical density

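### Non-adherence ends a subject's follow-up, not only intake, so the month-6 comparison of the randomised arms would lack non-adherent subjects unless their values are imputed

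*Protocol*

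**What the plan says.** Protocol section 5.1 sets the consequence of meeting a criterion: "Discontinue the study in the individual subject if the subject meets the following subject-specific discontinuation criteria". It then gives the reason for having the criteria: "The following discontinuation criteria are determined to secure the safety of the subjects and from the ethical viewpoint". Criterion 6 of section 5.2 is: "If the subject turns out not to have taken the investigational food as instructed by the investigator". No adherence threshold is attached to it.

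Section 5.4 has two items. The first is general: "Take measures necessary after the discontinuation". The second covers one group only: "For no show of unknown reason, the investigator will never fail to contact the subject within 4 weeks after the scheduled last administration". The purpose of that contact is to ask the subject to come in and to find out what happened.

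The primary variable in section 9.1 is "Changes in the macular pigment optical density". In Table 3 the row "Macular pigment measurement" is marked at baseline and at each of months 1 to 6, and blood is drawn at baseline, month 3 and month 6. The table has no early-termination column and no adherence check.

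**The concern.** The protocol does not distinguish a subject who stops or mishandles the capsules from a subject who leaves the study. Criterion 6 turns the first into the second. Incorrect intake of a food supplement is not obviously a safety or ethical matter, so the reason given in section 5.1 does not explain why follow-up should end.

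Adherence is observed after randomisation. The two products differ in suspension oil and in zeaxanthin content (section 4.7), so tolerability, and with it adherence, could differ by arm, although nothing in the protocol shows that it does. Section 2.1 sets an equivalence objective, for which a reader would want both an as-randomised comparison and one in adherent subjects. A later analysis plan can choose an analysis set, but it cannot supply month-6 observations that were never taken.

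**Working it through.** The protocol states no dropout rate, SD, margin or power, so there is no figure of its own to reproduce beyond the sample size: 3 per cell x 2 sexes x 3 age groups x 2 arms = 36, or 18 per arm, which agrees with Table 1. Everything below that uses an adherence rate is an assumption.

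**1. What is kept and what is lost.** Suppose a subject is removed under criterion 6 between months k and k+1.
- MPOD: baseline and months 1 to k are kept; months k+1 to 6 are not collected.
- Plasma lutein: removal before month 3 leaves no value after baseline; removal between months 3 and 6 leaves month 3 only.
- Month 6: no MPOD or plasma value in either case, unless someone arranges a measurement that the protocol does not mention.

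**2. How often this would happen (assumed non-adherence q, same in all subjects).** Expected number removed = 36q; chance of at least one = 1 - (1 - q)^36.

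| q | Expected removed | Chance of at least one |
| --- | --- | --- |
| 5% | 1.8 | 84% |
| 10% | 3.6 | 98% |
| 20% | 7.2 | >99.9% |

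**3. Possible shift in the contrast.** Let adherers in both arms have the same MPOD rise, set to 1. Let non-adherers lose a fraction r of it, with r = 0.5 (half the response) to r = 1 (none). With non-adherence qA and qB:
- As-randomised difference = (1 - qA r) - (1 - qB r) = (qB - qA) r.
- Adherers only: 1 - 1 = 0.
- qA = 5%, qB = 20%: 0.15 x 0.5 = 0.075, and 0.15 x 1 = 0.15, so 7.5% to 15% of the full rise.
- qA = 10%, qB = 30%, r = 1: 0.20.
- qA = qB: 0, whatever r is.

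**4. Precision.** 90% CI half-width in SD units = t(0.95; n1 + n2 - 2) x sqrt(1/n1 + 1/n2).
- 18 and 18: 0.564.
- 16 and 16: 0.600 (+6.5%).
- 14 and 14: 0.645 (+14%).
- 18 and 14, an uneven loss: 0.605 (+7.3%).

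**5. The no-show rule.** Administration lasts six months (section 4.9), so the latest contact date is about month 7. A subject who attends month 1 and first misses month 2 could wait about 5 months for contact; one who misses month 1 could wait about 6. The rule sets a latest date and does not bar earlier contact.

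**The case against.** A reader might infer that the trial becomes a compliers-only comparison and that an as-randomised analysis is impossible. The protocol does not support that. No section excludes discontinued subjects from analysis, and analysis sets and missing-data handling may stand in a statistical analysis plan that is not shown. MPOD is measured monthly, so a subject removed at month 4 or 5 still contributes baseline and several later readings. A repeated-measures analysis could include any subject with such readings, under an assumption about the missing ones. This objection stands, and it confines the point to outcomes after removal, chiefly month 6.

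Nor does the protocol forbid a closing measurement. The general item in section 5.4 could be read to include one, and the no-show item does ask for a visit. But the first names no measurement, and the second applies only to unexplained absence, not to a subject removed for incorrect intake.

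The 5% against 20% scenario has no source in the protocol. Both arms take one capsule daily under blinding, and little intolerance is expected (section 10), so similar adherence is plausible. The direction of bias is not fixed either. If 20% in each arm were non-adherent with no response, a true difference d among adherers would appear as 0.8d in the as-randomised comparison, which favours equivalence. The adherent-subject comparison is therefore a legitimate companion in this design. That too stands, and it is a reason to make both analyses possible.

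**Conclusion.** The point holds as a gap in the protocol. Sections 5.1 and 5.2 end follow-up for non-adherence, and section 5.4 and Table 3 provide no MPOD or plasma lutein measurement afterwards. Followed as written, the plan loses month-6 outcomes in a subset defined by behaviour after randomisation, and only imputation could fill them.

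The effect on the comparison is unknown. It is 7.5% to 15% of the full MPOD rise under the assumed 5% against 20% non-adherence, and nil if adherence is equal. The loss of precision is modest: 0.56 to 0.60 SD if 2 of 18 are lost per arm. The no-show timing is a secondary weakness, since the rule gives only an outer limit. The mismatch with the safety and ethics rationale is one of wording and has no numerical consequence. The change is worth making because it is cheap and the missing observations cannot be collected later.

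**What to change.** - In sections 5.1, 5.2 and 5.4, separate stopping intake from stopping follow-up. When intake stops remains for the investigators to decide.
- State that non-adherence alone (criterion 6) does not end follow-up. Ask these subjects, unless they withdraw consent, to keep the remaining MPOD and blood visits in Table 3, or at least month 6. This need not extend to subjects who cannot be examined or followed, or to adverse-event and accident cases.
- Record adherence, for example by capsule count, at the existing monthly visits, so that both an as-randomised and an adherent-subject comparison can be made. Which is primary can be left to the analysis plan.
- In section 5.4, tie no-show contact to the missed visit as well as to the scheduled last administration.

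The cost is a wording change, a capsule count at visits already scheduled, and a few retained visits.

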### 5.3. Whole or part of the study discontinuation criteria

1. If the investigator assesses it difficult to continue the study and that the study should be discontinued because of the onset of a serious AE
2. If the director of the study center instructs to discontinue the study

## 5.4 Procedures to follow after the discontinuation

1. Take measures necessary after the discontinuation. When the study is discontinued because of the AE, the investigator must take measures as appropriate irrespective of the reason.
2. For no show of unknown reason, the investigator will never fail to contact the subject within 4 weeks after the scheduled last administration to solicit the visit and investigate the outcome.

# 9. Evaluation (note; The number is mistaken in the original protocol written in Japanese)

## 9.1. Primary variable

Changes in the macular pigment optical density

### 9.2. Secondary variables

1. Changes in the far and near visual acuity
2. Changes in the contrast and glare sensitivity
3. Change in macular ERG
4. Changes in the plasma lutein level

# 10. Anticipated benefits and disbenefits of participation in the clinical study

Lutein intake is expected to improve the MPOD and plasma concentration of lutein. Lutein, which is a food ingredient, and no specific AE has been reported at the usual dose. The dose investigated is the usual dose of commercial products, therefore no AE is expected. It is speculated, however, some subjects complain gastrointestinal disorders such as constipation.

Measurement of MPOD is performed with mydriasis. There is a possibility of allergic reaction to mydriatic agents, and loss of accommodation for a few hours.

Taking blood sample is painful.

Investigational foods are supplied by supplement supplier. Study-related examinations and cost of measurement of the plasma lutein level will be covered by department of Ophthalmology, Seirei Hamamastu General Hospital. The subject will not incur any cost as a result of the participation in the study.

# 11. Procedures to follow after the study

The investigator will submit the study completion report to the director of the study center immediately after the completion of the study. Post-study procedures for individual subjects will be decided individually.

## **12** **Safety consideration**

Lutein and zeaxanthin contained in the capsule are nutritional ingredients of food. The dose of 10 mg/day is identical to the dose of previous study performed by Ritcher et al, and no adverse effects were reported.

Both supplements used in this study are same to products commercially available in Japan, and there have been no reports of adverse effects on these products.

The safety of Raman spectroscopy has been established for human usage. There were no adverse effects by using this device in our previous studies.

# 13. Ethical conduct of the study

The study is to be performed in accordance with the ethical principles based on the Declaration of Helsinki.

13.1. The study receives judgment on the study protocol and appropriateness of the investigators before the start of the study by the institutional review board. The study can start after the approval of the institutional review board.

## 13.2. Patient consent

The investigator will adequately explain the purpose and other details of the study using the explanatory and consent document approved in advance by IRB and supply the explanatory document to the subject prior to the start of the study. Obtain the subject's voluntary written consent to participate in the study. The subject and the investigator who has given the explanations will sign the consent document.

If the subject is assessed incapable of giving consent, disqualify the subject.

The investigator will provide the date of obtainment of consent in the CRF, have the subject sign the consent document in the relevant box unless otherwise agreed upon for the study center, supply the consent document to the subject, and submit the original of the signature page of the consent document to the IRB or other relevant department of the study center for storage.

After obtaining consent from the subject, the investigator or subinvestigator will allocate the subject number.

13.3. In the case of obtaining any information considered to affect the subject's willingness to continuously participate in the study, the investigator or subinvestigator will promptly supply the information to the subject, retain the record of information supply in the original medical record, and record the oral obtainment of re-consent. If any specific procedures are employed in the study center, retain the records according to the procedures. In the case of acknowledging the need to revise the explanatory and consent document based on the information, the investigator will discuss with the sponsor and make necessary revisions immediately. The investigator will submit the revised explanatory and consent document to the IRB by mediation of the director of the study center and gain approval. The investigator or subinvestigator will obtain the re-consent for the revised explanatory and consent document according to the procedures designated by the study center if any.

# 14. Study cost and interest

Study-related examinations and medical observations will not be assessed to health insurance. The investigational foods are supplied with free of charge. Seirei Hamamatsu General Hospital get grant from Koyo Mercantile Co., Ltd.

# 15. Availability of study-related compensation

The clinical study is to be performed based on the previous reports carefully according to the scientific protocol. If the subject has any ADR or health damage associated with the study during or after the completion of the study, the doctor will provide appropriate medical care and treatment.

The subject will not receive any remuneration. The subjects who completed the study receive commercial products of Koyo Mercantile Co., Ltd.

# 16. Agreement upon the release of data

The study data obtained in accordance with the study protocol belong to Seirei Hamamatsu General hospital. Release of the data will be discussed and decided by the supervisory investigator and all investigators. When the data are released, the privacy of the subjects will be kept confidential by anonymity.

# 17. Anticipated study period

July 1, 2010 to March 31, 2011

